| Safety evaluation    | Not applicable                                                                                                                                                                                                                                                                                                                                                    |
| Visit schedule       | Subjects will be scheduled to return to the clinic the next day if the vertigo and nystagmus will not resolve after two randomized maneuvers on the day of the visit.                                                                                                                                                                                             |
| Statistical analysis | Any difference in the treatment response would be determined using ANOVA and Chi-square test between the treatments and control groups.                                                                                                                                                                                                                           |
| Expected effects     | The head shaking and mastoid oscillation maneuvers would be recommended as initial treatment options for PC-BPPV-cu.                                                                                                                                                                                                                                              |

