## ▪ STUDY PROCEDURES

| Study procedure                     | V1              |               | V2 (V1+1day)                                                  |               |
|-------------------------------------|-----------------|---------------|---------------------------------------------------------------|---------------|
|                                     | Treatment group | Control group | Treatment group                                               | Control group |
|                                     |                 |               | When the subjects still have positional vertigo and nystagmus |               |
| Informed consent                    | X               | X             |                                                               |               |
| Demographics assessment             | X               | X             |                                                               |               |
| Inclusion/exclusion criteria        | X               | X             |                                                               |               |
| Medical history                     | X               | X             |                                                               |               |
| Assessment of dizziness history     | X               | X             |                                                               |               |
| Neuro-otological examinations       | X               | X             |                                                               |               |
| Positional test                     | X               | X             | X                                                             | X             |
| Canalith repositioning maneuver     | X               | X             |                                                               |               |
| Determination of treatment response | X               | X             | X                                                             | X             |
| End of study                        |                 |               | X                                                             | X             |

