## **7. METHODS**

### **1) STUDY METHODS**

- A. Subjects with PC-BPPV-cu confirmed and treated at each clinic will be randomly assigned to the treatment groups or to the control (sham) group.

- B. A treatment maneuver was performed by a physician according to the assigned treatments or sham group.
- C. Treatment response was determined by the participating neurologists at each clinic without knowing the maneuver applied to each patient 30 minutes after the initial maneuver.
- D. If the patient had positional vertigo and nystagmus, the previously applied maneuver was repeated.
- E. The patients underwent re-examination 30 minutes later and were scheduled for follow-up the next day without additional treatment if they still presented with positional vertigo and nystagmus.

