### **4) ASSESSMENTS**

- A. The absence of both vertigo and nystagmus was required to determine a resolution.

- B. Evaluation of treatment effect: The efficacy of treatment will be judged by an independent investigator blinded to the subject's information. If there is no improvement after the initial treatment, the patient will receive the same treatment once more. If there is still no improvement, the patient will visit the hospital again the following day for further evaluation.

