## **5) TRIAL ENDPOINTS**

- A. Primary endpoint: The overall short-term resolution rate of positional vertigo and nystagmus in the following day.
- B. Secondary endpoint: The immediate efficacy of two trials of each maneuver within 30 minutes.

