## 8. STATISTICS

### 1) DESCRIPTION OF STATICS METHODS

The demographic distribution of study participants by treatment maneuvers were compared using the Chi-squared test and one-way analyses of variance (ANOVA). If the results of the Chi-squared test were significant, additional post-hoc tests were performed using Bonferroni adjusted alpha level of 0.0167 per test (0.05/3). Statistical analyses were performed using SPSS (version 27.0; SPSS, Chicago, IL, USA).

The primary outcome was analyzed using both intention to-treat and per-protocol methods. Patients who did not complete the assessment in the following day were excluded from the per-protocol analysis.

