### **5) INCLUSION IN ANALYSIS**

The primary outcome would be analyzed using both intention-to-treat and per-protocol methods. Patients who can not successfully use the web-based system will be excluded from the per-protocol analysis.

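### As worded, the per-protocol rule removes every patient who resolves on day 1, because only day-1 failures are scheduled for the next-day assessment

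*Protocol*

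**What the plan says.** Section 8.1 analyses the primary outcome by intention-to-treat and by per-protocol, and defines the per-protocol set by one exclusion: "Patients who did not complete the assessment in the following day were excluded from the per-protocol analysis". Section 7.5 gives the primary endpoint: "The overall short-term resolution rate of positional vertigo and nystagmus in the following day".

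Four places say who gets a next-day assessment, and they agree:

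- Study Summary, in its row on visits: "Subjects will be scheduled to return to the clinic the next day if the vertigo and nystagmus will not resolve after two randomized maneuvers".
- Study Procedures table, condition over the V2 columns: "When the subjects still have positional vertigo and nystagmus".
- Section 7.1, item E: patients "were scheduled for follow-up the next day without additional treatment if they still presented with positional vertigo and nystagmus".
- Section 7.4, item B: "If there is still no improvement, the patient will visit the hospital again the following day for further evaluation".

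Section 8.5 repeats that both analyses will be done but gives a different per-protocol exclusion: "Patients who can not successfully use the web-based system will be excluded from the per-protocol analysis". Section 8.4 fills missing values by last observation carried forward. Neither section 8.1 nor section 8.5 says which analysis is primary.

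**The concern.** A patient whose vertigo and nystagmus clear on day 1 has no next-day assessment to complete. A rule that excludes everyone without that assessment therefore excludes every day-1 success and keeps only day-1 failures.

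This is selection on a post-randomization outcome, and one that treatment is expected to change. If a maneuver works, its arm loses more patients than sham does. Those who remain are the patients in whom it failed, compared with a less selected group of sham failures. The comparison is no longer randomized, and the difference within it is not the difference in the endpoint of section 7.5. A real benefit could show as no per-protocol difference, and with the two analyses unranked the protocol gives no rule for settling a conflict between them.

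The section 8.5 exclusion adds a separate drafting fault. The web systems described are those used for random assignment (Study Summary, study methods; section 7.3) and for issuing participant numbers (section 7.3). No procedure asks a participant to use one.

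**Working it through.** **Inputs.** From section 8.2: immediate resolution 70% in the treatment groups and 38% in sham, alpha 0.0167 (two-sided, since the formula uses Z at alpha/2), power 80%, allocation 1:1:1, dropout 5%, total 159. The Study Summary gives 53 per arm.

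**Step 1. Reproduce the plan's own figure.** With mean proportion 0.54, the section 8.2 formula gives

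n = [2.393 x sqrt(2 x 0.54 x 0.46) + 0.842 x sqrt(0.70 x 0.30 + 0.38 x 0.62)]² / 0.32² = 49.4, so 50 per arm.

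50 / 0.95 = 52.6, so 53 per arm, and 3 x 53 = 159. The stated size reproduces, and nothing here disputes it.

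**Step 2. Size of the per-protocol set under the literal rule.** Assumption: the 70% and 38% are day-1 rates after up to two maneuvers. Section 8.2 calls them immediate rates from a previous study and does not say how many maneuvers they follow. If they follow one, the cumulative day-1 rates could only be the same or higher, and the loss the same or larger.

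| Arm | Resolved day 1 (excluded) | Unresolved day 1 (kept) |
|---|---|---|
| Head shaking | 53 x 0.70 = 37.1 | 53 x 0.30 = 15.9 |
| Mastoid oscillation | 53 x 0.70 = 37.1 | 53 x 0.30 = 15.9 |
| Sham | 53 x 0.38 = 20.1 | 53 x 0.62 = 32.9 |
| Total | 94.3 (59%) | 64.7 (41%) |

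This is before any dropout.

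**Step 3. What each analysis would estimate.** Let q be the overnight resolution rate among day-1 failures, assumed equal in all arms. The protocol gives no value, so a range is shown. Next-day resolution in an arm with day-1 rate p, counting day-1 responders as resolved, is p + (1 - p)q. The true difference is therefore (0.70 - 0.38) x (1 - q). In the per-protocol set each arm resolves at rate q, so the difference is 0.

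| q | Active, all patients | Sham, all patients | True next-day difference | Per-protocol difference |
|---|---|---|---|---|
| 0.1 | 73.0% | 44.2% | 28.8 points | 0 |
| 0.3 | 79.0% | 56.6% | 22.4 points | 0 |
| 0.5 | 85.0% | 69.0% | 16.0 points | 0 |

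**Step 4. Power if the failures did differ by arm.** Both scenarios are assumptions. One active arm (16) is compared with sham (33) at two-sided 0.0167, by normal approximation.

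- 50% vs 30% overnight: standard error sqrt(0.25/16 + 0.21/33) = 0.148, and 0.20/0.148 - 2.393 = -1.04, so power is about 15% (unpooled 14.8%, pooled null 15.4%).
- 70% vs 38% overnight: about 38% with a pooled null variance and 44% unpooled. For the same two rates, 53 per arm gives 83% (pooled).

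**The case against.** The strongest reply is that the sponsor meant patients who were due back and did not attend. Two features support this. The endpoint is called an *overall* rate, which suggests that day-1 resolutions count. The sample size allows for 5% dropout, which no one expecting to discard 59% would write. On that reading the set is about 150 patients (roughly 50 per arm) and the bias goes. This stands as a likely intention, so a reader should not infer that the sponsor planned to analyse failures only. It does not rescue the text: the sentence makes no exception, and no other section treats day-1 responders as completers. A rule that admits a set of either about 65 or about 150 needs settling before the data are seen.

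A reader might also infer that the main result is compromised. The documents do not support that. The exclusion applies only to the per-protocol set, and last observation carried forward would carry a day-1 resolution into the intention-to-treat analysis. That imputation fills in values, however, and does not reverse an exclusion. Per-protocol is usually supportive in a superiority trial, but this protocol does not say so.

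A third tempting inference is that a 32-point effect on the primary endpoint vanishes. The 32 points are the assumed day-1 difference. The next-day difference equals it only at q = 0, when no day-1 failure resolves overnight.

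Finally, sections 8.1 and 8.5 do not contradict each other in logic, since two exclusions can both apply. The section 8.5 rule neither causes nor worsens the loss of responders.

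Leaving the matter to the statistical analysis plan is no answer: the protocol states the rule, and a later plan would have to depart from it.

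**Conclusion.** The point holds, tied to the literal wording. Section 8.1 and the visit schedule together yield a per-protocol set made up only of day-1 failures. If the section 8.2 rates hold after up to two maneuvers, 59% of patients are lost, at 70% in each active arm and 38% in sham. With equal overnight resolution the analysis then estimates 0 against a true next-day difference of 28.8 to 16.0 points for q from 0.1 to 0.5. The power figures are illustrations that move with the assumed overnight rates. That selection is on outcome and differs by arm needs only day-1 resolution rates that differ by arm. The sample size is unaffected, and so is the intention-to-treat analysis as regards this exclusion. Because the protocol commits to both analyses of the primary outcome without ranking them, the sentence should be corrected before analysis.

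**What to change.** 1. Reword the section 8.1 exclusion. Patients resolved at V1 count as completers with outcome resolved. Only patients who were due at V2 and were not examined leave the per-protocol set.
2. Delete the web-based-system exclusion from section 8.5, so that one per-protocol definition remains.
3. State that intention-to-treat is the primary analysis and per-protocol is supportive.

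The cost is a wording amendment, carried into the statistical analysis plan. It needs no extra visits, data or patients, and no change to the sample size or to patient management.

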### 2) THE NUMBER OF PARTICIPNATS

The following are assumed to calculate the sample size.

- A. Level of significance,  $\alpha=0.0167$
- B. The ratio of the treatment and control group = 1:1:1
- C. Power of the test,  $1-\beta = 80\%$
- D. In a previous study, we estimated that the proportions of patients with immediate resolution in PC-BPPV would 70% in the treatment groups, and 38% in the sham group.
- E. The formula for calculating the number of samples and the calculation results are as follows.
  - i.  $n1=n2=[Z_{\alpha/2} \sqrt{2\bar{P}(1-\bar{P})} + Z_{\beta}\sqrt{P_1(1-P_1)+P_2(1-P_2)}]^2 / (P_1-P_2)^2$
  - ii.  $n1$ = Sample size in the control group
  - iii.  $n2$ = Sample size in the treatment group

- iv.  $p_1, p_2$  = Expected outcome rates for each group
- G. Based on these estimations, a sample size of 159 participants is obtained with a dropout rate of 5%.
- H. The calculated sample size considers the drop rate, and in actual clinical research, more or fewer participants may be required than the calculated number of study subjects. When 30%, 60%, or 90% of the expected study subjects are achieved, a Data and Safety Monitoring Board meeting will be held to determine whether the number of participants is appropriate.

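### The per-protocol rule requires a next-day assessment that the schedule gives only to day-1 failures, so as worded it drops every day-1 responder, although a narrower exclusion was probably meant

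*Protocol*

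**What the plan says.** The primary endpoint (protocol section 7, 5)) is: "The overall short-term resolution rate of positional vertigo and nystagmus in the following day". On its analysis, section 8, 1) states "The primary outcome was analyzed using both intention to-treat and per-protocol methods" and then defines the second set by exclusion: "Patients who did not complete the assessment in the following day were excluded from the per-protocol analysis". No exception is made for any group.

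The protocol says consistently who has a next-day assessment:

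- Study Summary, in the row on visits: "Subjects will be scheduled to return to the clinic the next day if the vertigo and nystagmus will not resolve after two randomized maneuvers". Step 5 of the study methods in the same summary says the same.
- Study Procedures table, heading over the V2 columns: "When the subjects still have positional vertigo and nystagmus".
- Section 7, 1), item E: participants "were scheduled for follow-up the next day without additional treatment if they still presented with positional vertigo and nystagmus".
- Section 7, 4), item B: "If there is still no improvement, the patient will visit the hospital again the following day for further evaluation".

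No section schedules a next-day assessment for a participant who resolved on day 1. Section 8, 4) prescribes last observation carried forward for missing values. Section 8, 5) gives a different per-protocol exclusion, based on failure to use the web-based system.

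**The concern.** A per-protocol set is meant to select on adherence. Here membership depends on having an assessment, and whether a participant has it is decided by the result of treatment: only a day-1 failure is called back. Taken at its word, the rule keeps the failures and discards the successes.

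The per-protocol analysis is one of two planned analyses of the primary outcome, and the protocol ranks neither above the other. An analyst who follows the sentence literally would report, beside the intention-to-treat result, a comparison in which no day-1 response can appear. An analyst who departs from it has no written rule for who belongs in the set, and may have to choose after seeing the data.

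**Working it through.** **Inputs.** From section 8, 2): "the proportions of patients with immediate resolution in PC-BPPV would 70% in the treatment groups, and 38% in the sham group"; two-sided α = 0.0167; power 80%; allocation 1:1:1; dropout 5%; total 159. From the Study Summary: 53 per arm. I take the 70% and 38% as the proportions resolved by the end of day 1. The protocol gives no rate of overnight resolution among day-1 failures (q below) and no rate of missed next-day visits (m below), so both are assumptions shown over a range.

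**Step 1: the plan's own figure.** With P̄ = (0.70 + 0.38)/2 = 0.54:

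n = [2.393·√(2·0.54·0.46) + 0.842·√(0.70·0.30 + 0.38·0.62)]² / 0.32² ≈ 49.4, so 50 per arm.

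50/0.95 = 52.6, so 53 per arm, and 3 × 53 = 159. The stated sample size reproduces exactly and is not in question. It rests on a 32-point difference in day-1 resolution.

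**Step 2: who survives the literal rule.**

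| Arm | Randomised | Resolved on day 1 (removed) | Day-1 failures (kept) |
|---|---|---|---|
| Head shaking | 53 | 53 × 0.70 = 37.1 | 15.9 |
| Mastoid oscillation | 53 | 37.1 | 15.9 |
| Sham | 53 | 53 × 0.38 = 20.1 | 32.9 |
| Total | 159 | 94.3 | 64.7 (41%) |

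Day-1 resolution in the kept set is 0% in every arm, so the planned 32-point contrast is 0.

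**Step 3: what the literal set can still show.** In all randomised participants the next-day rate is r + (1 − r)q, where r is the day-1 rate. In the literal set it is just q.

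| Assumed q, active v sham | Difference, all randomised | Difference, literal set | Power, literal set |
|---|---|---|---|
| 20% v 20% | 76.0% − 50.4% = 25.6 points | 0 | – |
| 20% v 10% | 76.0% − 44.2% = 31.8 | 10 | about 10% |
| 30% v 10% | 79.0% − 44.2% = 34.8 | 20 | about 29% |
| 50% v 20% | 85.0% − 50.4% = 34.6 | 30 | about 41% |
| 10% v 20% | 73.0% − 50.4% = 22.6 | −10 | – |

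With equal q anywhere from 0% to 30%, the difference in all randomised runs from 32 down to 22.4 points, and the literal set always gives 0.

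**Step 4: the narrower reading.** Suppose only recalled participants who do not attend are excluded, a fraction m of day-1 failures in each arm. The per-protocol rate is [r + (1 − r)(1 − m)q] / [r + (1 − r)(1 − m)]. With q = 20% in every arm the undistorted values are 76.0%, 50.4% and 25.6 points.

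| m | Active | Sham | Difference | Shrinkage |
|---|---|---|---|---|
| 10% | 0.754/0.970 = 77.7% | 0.4916/0.938 = 52.4% | 25.3 | 0.3 |
| 20% | 0.748/0.940 = 79.6% | 0.4792/0.876 = 54.7% | 24.9 | 0.7 |
| 30% | 0.742/0.910 = 81.5% | 0.4668/0.814 = 57.3% | 24.2 | 1.4 |

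Each arm's rate is inflated by about 2 to 7 points. The inflation is larger in sham, where 62% rather than 30% of participants are exposed to exclusion.

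**Step 5: is it repaired elsewhere?** Carrying the last observation forward fills in a value but does not return an excluded participant to the set. The web-based-system exclusion in section 8, 5) is a different criterion and leaves this one standing.

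**The case against.** The best defence is that nobody intended the literal reading, and the protocol supports this. An overall resolution rate by the following day has to count day-1 resolutions and cannot be computed in a set that contains none. A plan with 5% dropout does not sit with a rule that removes 59% of participants (94.3/159). Failing to complete an assessment most naturally describes someone who was due one. If the whole planned dropout (0.05 × 159 ≈ 8) fell on the roughly 65 day-1 failures, m would be about 0.12, and the step 4 formula gives a difference of about 25.2 points, a shrinkage of about 0.4. I accept this as the likely intent, and on it the numerical effect is small.

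A reader might also infer from the literal rule that the per-protocol analysis must come out null or reversed. The documents do not support that. The loss is exact only for the day-1 component. A zero difference requires equal overnight resolution in all arms, and a reversal requires active-arm failures to do worse overnight than sham failures; the protocol gives no figures for either. Nor is the trial's main comparison damaged: intention to treat keeps everyone randomised, and a day-1 resolution is carried forward under section 8, 4).

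What the defence does not remove is the sentence itself. It states a definite rule with no exception, and that rule conflicts with the protocol's own schedule. This is more than a detail left for a statistical analysis plan to supply.

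**Conclusion.** The point holds as a conflict between the per-protocol rule and the visit schedule. Followed literally, the rule keeps about 65 of 159 participants, all selected for having failed on day 1, and excludes the 32-point contrast on which the trial was sized. Any difference left in that set concerns overnight resolution among failures, with arms of about 16 against 33. These counts rest only on the protocol's planning rates.

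Under the reading probably intended, the distortion is about 0.3 to 1.4 points toward no difference, given the assumed 20% overnight resolution and 10% to 30% missed visits. The intention-to-treat analysis and the sample size are sound on either reading. It would go too far to say that the plan erases the treatment effect: that holds only for the day-1 part of the effect, in one of two analyses, under the less likely reading. The wording still needs correcting before analysis, because the rule as written gives a wrong per-protocol result.

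**What to change.** Replace the exclusion sentence in section 8, 1) with wording such as: *Participants resolved on day 1 remain in the per-protocol set and are counted as resolved; only participants scheduled for the next-day visit who did not attend are excluded.*

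Reconcile section 8, 5) with it, so that the protocol carries one per-protocol definition and either drops the web-based-system criterion or states how it combines with this one.

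The narrower exclusion still removes only day-1 failures, and proportionately more of them from sham. Add a sensitivity analysis that keeps these participants in the set, once with all of them counted as resolved and once with none.

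The cost is one reworded sentence, the matching edit to section 8, 5), and one extra analysis. No new data, visits or participants are needed.
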